**Sitting, standing or breaking: Which is better for cardio-metabolic health?**

**A randomised cross-over study**

**Funding Agencies:** University of Otago Research Grant

**Principal Investigator:** [name]^1^

**[contact]

**Email:** [[contact]](mailto:[contact])

**Co-investigators:** [name]^2^

Associate [name]^3^

[name]^3^

^1^Department of Human Nutrition

^2^Surgical Sciences, Dunedin School of Medicine

^3^School of Physical Education, Sport ad Exercise Science

University of Otago

[name]

Dunedin

New Zealand

1. **Project Summary**

This study will provide important evidence around how reducing sedentary behaviour by standing, or performing short bouts of activity regularly may improve postprandial metabolism and endothelial function, both of which are important for cardio-metabolic health. We will conduct a randomised cross-over study involving 18 healthy, normal weight participants. The study will include three experimental intervention sessions: prolonged sitting; prolonged standing; and regular activity breaks, each separated by a minimum six-day washout period. Flow-mediated dilation will be measured at baseline, and at the conclusion of each intervention, while popliteal artery haemodynamics will be measured hourly to assess changes in blood flow and shear stress. Area under the curve will be calculated for plasma glucose and insulin. Mixed model regression will be used to examine differences in the effect of the three different interventions on markers of endothelial function and postprandial metabolism**.**

**2. Background**

Sedentary behaviour – activities performed in a seated or reclining position that involve very low energy expenditure (1) – predominate the waking hours of many adults. Recently we measured, using two different validated accelerometers, the sedentary behaviour patterns of 79 University of Otago employees and found, on average, they spend 75% of their workday sitting down (2). An increasing number of large-scale prospective studies have shown that sedentary time is associated with increased incidence of diabetes and cardiovascular disease and overall mortality (3, 4). Interestingly, the results of a recent meta-analysis indicate that only when 60-70 min of physical activity is performed on a daily basis are the negative consequences of sedentary behaviour overcome (5). This is a level of physical activity far above that of the University employees surveyed, despite many of them meeting currently physical activity guidelines (2).

Most intervention studies designed to test the causality of the association between sedentary behaviour and health outcomes have focused on the *acute* effects of regularly interrupting periods of prolonged sitting with short bouts of activity on postprandial metabolism. Indeed, our research group was among the first to provide experimental evidence indicating that breaking up periods of prolonged sitting with regular short bouts of activity markedly attenuates the rises in postprandial glucose and insulin concentrations observed with long periods of uninterrupted sitting, and that this attenuation is greater than that seen with a single bout of 30 min of continuous activity (6). A growing number of studies have now been conducted in this area, confirming that ~1.5 min – 5 min of light or moderate activity performed every 20 – 30 min can improve postprandial glucose metabolism when compared to 2 – 9 h of uninterrupted sitting in participants ranging from healthy inactive young adults to those who have obesity and type 2 diabetes (6-9). An alternative method for reducing prolonged sitting is to encourage standing. However, the evidence suggesting that standing desks are the best method for combating the perils of too much sitting lags markedly behind the recent explosion in sales of standing workstations (10). The results of a small number of acute studies indicate that short bouts of standing (11) or even alternating 30 min of standing with 30 min of sitting (12) are not as effective at reducing postprandial glycaemia as regular *activity* breaks, particularly in healthy, normal weight populations (11). Very little is known about the effects of more prolonged bouts of standing, despite recommendations being made to encourage individuals to stand for at least half of their work day (13).

The results of two recent studies performed using participants who have type 2 diabetes indicate that performing regular activity breaks over a seven-hour period during the day results in sustained improvements in nocturnal glycaemic control after the participant has left the laboratory (14, 15). However, it is not clear whether these effects would be observed in healthy people, or how long the improvements in glycaemic control are maintained. In addition, we have very little information about whether after a sustained period of performing regular activity breaks, or prolonged standing, individuals are likely to alter their activity levels to compensate for these different behaviours.

Endothelial function is an important and independent risk factor for cardiovascular disease and mortality (16). Change in localised haemodynamic forces (the forces associated with changing blood flow) play an important role in the development of endothelial dysfunction and atherosclerosis (17). Prolonged sitting reduces blood flow to the lower limbs, lowering shear stress (the force applied to the endothelial surface in the direction of the flowing blood), and resulting in transient endothelial dysfunction (18). Additionally, a greater volume of sedentary behaviour has also been associated with more permanent changes in endothelial function over time (19). It is likely that reductions in blood flow and endothelial function also contribute to the elevated postprandial glycaemia and lipidaemia observed with prolonged sitting given that muscle provides the largest source for glucose disposal, and that muscle prefusion facilitates glucose uptake. Reduced blood flow to the large muscles of the leg thereby reduces the major role those muscles can play in the regulation of glucose and lipid metabolism. To date, the results of two studies have indicated that both regular activity breaks (20) and standing (21) may protect against the negative impact sitting has on endothelial function. However, in both these studies the intervention period lasted only 3 hours, a duration of sitting much less than that accumulated during a usual work day (2). Additionally, there is some contrasting evidence to suggest that continuous standing may contribute to atherosclerosis progression in carotid arteries (22) – a result that would not be expected if standing was indeed having positive effects on blood flow and shear stress.

**3. Aim of Study**

To compare the effects of prolonged sitting, prolonged standing and sitting interrupted with regular short bouts of activity on postprandial glucose metabolism and endothelial function (via flow-mediated dilation).

**4. Objectives**

To compare sitting, standing and performing regular activity breaks for 6.5 h on their respective effects on

- flow mediated dilation and haemodynamics of the superficial popliteal artery;
- glucose and insulin AUC and iAUC; and
- the ensuing 48-h glucose profile and free-living activity patterns.

**5. Hypothesis**

We hypothesise that regular activity breaks, but not prolonged standing, will improve both endothelial function and postprandial glucose metabolism when compared to prolonged sitting.

**6. Study Design**

This study will be a randomized, three-way cross over trial, in which each participant will complete three 6.5-h intervention sessions: 1) Prolonged Sitting; 2) Prolonged Standing; and 3) Regular Activity Breaks, in which sitting will interrupted every 30 min with a 2-min bout of activity. Each intervention session will be separated by at least 6 days.

**7. Study Setting/ Location**

This single site study will be conducted in the School of Physical Education, Sport and Exercise Science at the University of Otago’s Dunedin Campus.

**8. Study Population**

18 healthy, normal weight adults between 18 and 40 years of age.

**9. Eligibility Criteria**

Participants in this study are required to be predominantly sedentary during the day, therefore we will require participants to:

- Self-report spending greater than 5 h per day, on average, engaged in sedentary behaviour;
- Not be currently using a sit-to-stand workstation on a regular basis.

Other research indicates that the effects of regular activity breaks on postprandial metabolism differ in people of different weight and health status (23), therefore, participants will only be included in the study if they:

- Have no personal history of cardiovascular disease or diabetes;
- are a non-smoker;
- Have a BMI of less than 35 kg·m^2^.

Because we are measuring postprandial glucose metabolism and endothelial function, which can be effected by medications, and dietary supplements, participants will also only be included if they are:

- Not taking any medication, dietary supplements, vitamins or minerals other than oral or other hormonal contraceptive agents.

We will also ask participants not to take part if:

- They have been told by a doctor that they should avoid doing physical activity or standing for long periods (because they will be asked to do both of these things in the study);
- They have an intolerance or allergy to dairy or gluten as the test meal and snack will contain these foods.

Participants will be excluded from participating if their Physical Activity Readiness Questionnaire (PAR-Q) data indicate that participating in physical activity may not be appropriate, or if their mean blood pressure measurement taken in the screening visit is greater than 140/90 mm Hg.

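### The population is described as normal weight, but the only weight criterion is BMI below 35 kg/m², so people outside that description could be enrolled

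*Protocol*

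**What the plan says.** The Protocol describes its population in two places. Section 1 (Project Summary) announces a "randomised cross-over study involving 18 healthy, normal weight participants". Section 8 (Study Population) consists of one line: "18 healthy, normal weight adults between 18 and 40 years of age".

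Section 9 (Eligibility Criteria) then gives a reason for limiting entry. It says other research indicates that "the effects of regular activity breaks on postprandial metabolism differ in people of different weight and health status", and from this it derives three inclusion criteria: no history of cardiovascular disease or diabetes, non-smoking, and "Have a BMI of less than 35" kg/m². Only the third concerns weight. The other exclusions in Section 9 concern daily sitting, standing-desk use, medication and supplements, medical advice against activity or standing, food intolerance, the PAR-Q and blood pressure. At the screening visit (Section 11) height and weight are measured, but no further weight limit is attached to them.

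**The concern.** The label and the criterion describe different groups of people. Recruitment in Section 11 asks volunteers to confirm that they meet the eligibility criteria, so in practice Section 9 decides who enters. A volunteer with a BMI of 32 passes every weight check in the document, although Sections 1 and 8 say the trial studies normal weight adults.

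The limit also fails to deliver what Section 9 gives as its purpose. If the effect on postprandial metabolism depends on weight, a limit that lets in overweight and part of the obese range does not hold weight constant. Two things are at stake: to whom the results apply, and whether the glucose and insulin comparisons average over groups that the plan expects to respond differently.

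**Working it through.** This is mainly a comparison of text, with a small amount of arithmetic to show how wide the gap is.

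**Step 1: set the statements side by side.**

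| Place | Statement on weight |
|---|---|
| Section 1 | normal weight |
| Section 8 | normal weight |
| Section 9, reason | effects on postprandial metabolism differ by weight, so entry is restricted |
| Section 9, criterion | BMI below 35 kg/m², no lower bound |
| Section 11, screening visit | height and weight measured, no added limit |

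No section defines normal weight numerically, and none closes the gap between the label and the limit.

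**Step 2: what the limit admits.** The conventional adult bands are assumed: normal below 25, overweight 25 to below 30, obesity from 30. A limit of below 35 then admits all of the overweight band and obesity from 30 to below 35. BMI 35 itself is excluded.

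**Step 3: the same in kilograms.** Weight = BMI × height². At an assumed height of 1.70 m, height² = 2.89:

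- BMI 25: 25 × 2.89 = 72.3 kg
- BMI 30: 30 × 2.89 = 86.7 kg
- BMI 35: 35 × 2.89 = 101.2 kg

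At that height the criterion reaches about 29 kg beyond the assumed upper edge of normal weight (101.2 − 72.3 = 28.9). This shows the width of the limit. It does not predict who will volunteer.

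**Step 4: does the plan treat weight as relevant?** Section 9 says so for postprandial metabolism. Section 2 (Background) also singles out healthy, normal weight populations when it reports that standing is less effective than activity breaks at lowering glycaemia, and it places people with obesity and type 2 diabetes at the other end of the range already studied.

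**Step 5: which outcomes are touched?** In Section 10 glucose and insulin AUC and iAUC are secondary outcomes. The primary outcome is the change in flow-mediated dilation, and the protocol nowhere says that this effect varies with weight.

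**Step 6: the sample size.** The 18 participants in Section 12 cannot be reproduced, because no standard deviation or within-person correlation is given. The contradiction does not depend on that figure.

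**The case against.** The strongest reply is that the words normal weight may simply be a loose descriptor. They appear as a population label only in Sections 1 and 8. The aim, objectives, hypothesis and significance statement (Sections 3, 4, 5 and 14) do not confine the inference to normal-weight people, and Section 14 speaks of public health guidance in general. This stands in part: the documents do not show whether the label or the limit is the mistake. It does not reconcile them.

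A second reply is that each participant is their own control, so weight differences in outcome level drop out of the comparisons. That is right for level. It does not remove differences in response to the interventions, which is what Section 9 says varies with weight.

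Some stronger readings are tempting and are not supported:

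- **That the primary analysis is compromised.** The weight rationale covers postprandial metabolism only.
- **That power is lost.** A wider BMI mix might add variation in response, but no standard deviation is stated and the size of any such variation is unknown. Any figure for lost power would rest on an invented inflation.
- **That heavier people will be enrolled, or will form a given share of the 18.** They could be. The documents give no BMI distribution for the campus recruitment pool.
- **That the age range is missing.** Section 8 states 18 to 40 years and nothing contradicts it. Its absence from the list in Section 9 is a matter of tidiness.

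**Conclusion.** The contradiction holds. The stated population is normal weight, and the operative criterion admits overweight and obesity up to just below BMI 35. The criterion therefore does not achieve the restriction that Section 9 offers as its reason. The conclusion assumes only the conventional BMI bands. The protocol's silence on a numerical definition does not rescue the text, because BMI 30 to below 35 is not normal weight under any usual definition.

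The consequence is for the stated applicability of the results and for possible mixing of responses in the glucose and insulin outcomes. How large that mixing would be cannot be derived from the document. The point still needs correcting, because eligibility decides who is enrolled and an analysis plan cannot change that afterwards.

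**What to change.** Reconcile Sections 1, 8 and 9 by a short amendment, in one of two ways:

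1. **If normal weight is intended:** state the sponsor's numerical definition of it and set the BMI limit in Section 9 to match. The cost is a smaller recruitment pool, by an amount the documents do not allow one to estimate.
2. **If BMI below 35 is intended:** remove normal weight from Sections 1 and 8, correct the rationale in Section 9, and do not describe the results as applying to normal-weight adults. The edit itself is trivial. It corrects the stated applicability but leaves any variation in response by weight in the data.

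The choice belongs to the sponsor and should be made before enrolment, because once people outside the label have been enrolled only the label can be corrected. The age range of 18 to 40 years can be added to the Section 9 list in the same amendment, as tidying only.

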**10. Study Outcomes**

Primary Outcome: The difference in the change in flow-mediated dilation taken at 0 and 6 h between the three different interventions

Secondary Outcomes

1. The difference in the change over time in superficial femoral artery hemodynamics between the three different interventions.
2. The difference in glucose AUC and iAUC between the interventions.
3. The difference in insulin AUC and iAUC between the interventions.
4. The difference in the continuous glucose profile in the 48 following the interventions
5. The difference in free living activity patterns in the 48 h following the interventions

**11. Study Procedures**

Recruitment of participants

Paper and electronic copies of the recruitment flyers advertising the study will be distributed around the university campus. Individuals interested in participating will be asked to indicate interest by emailing [contact]. The postgraduate research students involved in the study, or the PI ([name]) will respond to the email providing a copy of the information sheet and asking them to confirm that they meet the eligibility criteria. Participants who do not meet the eligibility criteria will be informed of this and thanked for their interest. Participants who apparently meet the eligibility criteria, and are still interested in participating upon reading the information sheet will be scheduled to attend an initial consent and screening visit at the Department of Human Nutrition. Recruitment will continue concurrently with data collection until 18 participants have completed the study.

Randomisation

Participants will be block randomized (block size n=6) to complete the three interventions in 1 of 6 possible orders. The randomization sequence will be generated by [name] using STATA software and concealed electronically. The evening before each participant begins his or her first intervention session [name] will reveal and assign the next sequential randomization. Participants will not be notified of which intervention session they are completing until the arrive at the clinic on the morning of each intervention session. However, by a process of elimination they will know what their third and final intervention will be as soon as they begin their second intervention session.

Study procedures

***Screening visit***

Once written informed consent has been obtained from the participant they will complete a questionnaire that asks their:

- Demographic information
- Heath history and status
- Physical Activity Readiness (PAR-Q)
- Usual physical activity patterns
- If they have an allergies/intolerances/strong dislikes of the study food

The participant will then have their height, weight and blood pressure (in triplicate 1 min apart; after 15-min seated rest) measured.

***Standardization of Prior Physical Activity and Diet***

To minimise the influence of previous activity on outcome measures, participants will be required to avoid all intentional moderate-to-vigorous intensity physical activity and be largely sedentary for 24 h prior to each intervention. In the 24 h before their first testing session, participants will be required to complete a 24-h diet record, in which they will record all food and beverages including caffeinated beverages. They will also be fitted with an accelerometer and interstitial glucose monitor to be worn for the following four days (from the day before the intervention through until 48 h post intervention). The diet record will be returned to participants 24 h prior to each subsequent intervention session, when they will also be refitted with an accelerometer. They will then be asked to replicate the recorded diet (including the timing of eating), and abstain from alcohol consumption 24 hours prior to each intervention. The intervention session will commence only if participants can verify their compliance with these protocols.

Upon completion of the intervention session participants will be free to leave the laboratory, but will continue to wear both the accelerometer and the glucose monitoring system for 48 h after the intervention. At completion of the 48 h period participants will return to the clinic to have accelerometer and glucose monitor removed.

[figure not shown]

**Figure One:** Intervention session timelines

Measurements

***Measurement of superficial popliteal artery haemodynamics***

Popliteal artery (PoPA) diameter and blood velocity will be measured using ultrasound (Terason uSmart 3300, MA, USA) with a 15 MHz lineal array transducer (bandwidth 4-15 MHz) by simultaneously recording a longitudinal section B-mode image and a spectral Doppler trace of blood velocity. The Doppler angle of insonation will be maintained at ≤60°. Measurements will be made in the popliteal fossa with the participant in a semi-recumbent position, in the prolonged sitting and regular activity breaks interventions, and in a standing position in the prolonged standing intervention. The position will be marked on the skin with permanent ink to ensure the same location is used for each measurement. Locations will be measured from bony landmarks and/or the knee skin crease and replicated between protocols. Ultrasound depth, focus position and gain will be optimised for each participant for the first measurement and the same settings used each subsequent measurement. Video clips will be recorded using Camtasia Studio Screen Recording Software (TechSmith, MI, USA). Analysis of diameter and velocity, and calculation of shear rate will be performed using wall-tracking software (Cardiovascular Suite v 3.4, Quipu, Pisa, Italy). Haemodynamics will be assessed for ~60 seconds on each occasion. Ultrasound scans will be performed by one of the investigators (KT), and possibly one of the research students who will have extensive training in vascular sonography – however all the measurements performed on a participant (across all interventions) will performed by the same sonographer.

***Measurement of Flow-Mediated Dilation (FMD*)**

Flow-mediated dilation is a measure of endothelial function, which is based on the ability of the vessel to vasodilate in response to transient ischaemia. Transient ischaemia will be induced by inflating a 12 cm cuff around the mid-calf 200 mm Hg within 2 seconds (SC12 contoured leg cuff, E20 Rapid Cuff Inflator and AG101 Cuff Inflator Air Source, Hokanson, Bellevue WA, USA). Occlusion will be maintained for 5 min and recording will be continued for 3 min following rapid release of the cuff. Baseline diameter (D_base_), blood flow velocity (v) and shear rate (SR) will be calculated as the mean of the last minute of recording prior to cuff inflation. Peak diameter post-deflation will be determined automatically using the edge-detection software. Flow-mediated dilation will be calculated as the percentage increase in diameter from the baseline (FMD = (D_peak_-D_base_) / D_base_ x 100), following guidelines utilising allometric scaling to adjust for D_base_ with a covariate-controlled approach (24)

